### Registration

The trial is promoted by Fondazione Policlinico A. Gemelli IRCCS, Rome (Italy). The clinical and investigational procedures will be based on approval from the local ethics committee. Each interested center will submit the protocol to its ethics committee for approval before accrual. After approval, the center will receive a dedicated electronic case report form (CRF). Eligible participants who provide consent and meet the inclusion criteria are anonymously registered in the CRF by assigning a numerical code. Final stratification of the enrolled patients will be performed globally to enhance the homogeneity and balance of the final dataset.

### Ethics considerations

The trial will be conducted in compliance with the approved protocol, Declaration of Helsinki 2008, principles of Good Clinical Practice (GCP), and Italian National Normative for clinical experimentation. Upon signing the protocol, every investigator will provide consent for the procedure and instructions in the protocol and run the study according to the GCP, Declaration of Helsinki, and National Normative. Every amendment to the study will be registered and submitted to the ethics committee. Our trial protocol and its attached material have been approved by the Ethics Commission of Fondazione Policlinico Gemelli IRCCS (Rome, Italy). Every participant center must submit our protocol to their respective ethics commission before enrolling patients.

## Discussion and final considerations

Sustained monomorphic VT is a potentially life-threatening condition that often affects patients with structural heart diseases. VT recurrence poses a severe threat to health and quality of life. Long-term management of recurring VT relies mainly on ICDs, pharmacological control (i.e., class III antiarrhythmic), and RFA of the pathological arrhythmogenic substrate.

New long-term solutions are currently being sought for patients in whom VT is refractory to conventional treatment strategies or in whom it cannot be performed. In patients with structural heart disease, the rate of VT recurrence after RFA has been reported to be between 25 and 50% (8). Intrinsic technical aspects of the procedure (e.g., difficult anatomical location of the arrhythmic substrate) as well as patient-related factors (e.g., patient frailty) may limit RFA feasibility in a portion of the population. Patients with structural heart disease are often fragile and have a varying number of comorbidities. Therefore, procedure invasiveness could be a limiting factor in the choice of the best treatment strategy (9).

Cuculich et al. first investigated the efficacy and safety of stereotactic radiation for the ablation of VT in a five-patient case series, which was later followed by the publication of a phase I/II prospective study by the same authors, including 19 patients (1, 2). Both studies reported a statistically significant reduction (99.9 and 94%, respectively) in VT episodes after a blanking period of 4 weeks. Subacute and chronic treatment-related side effects ranged from asymptomatic pericardial effusion to radiation-induced pericarditis and pneumonitis and were successfully treated with corticosteroids. Since then, a growing number of scientific articles have been published on this matter.

Overall, VT-ART has been proven to be an effective and adequately safe intervention in other studies (10, 11). Its non-invasive nature makes it a safe alternative for patients who are not suitable for percutaneous RFA (9). Nevertheless, despite the promising results detected by sporadic reports, limited case series, and systematic reviews (12), we still do not know if and at what level VT-ART (and STAR in general) could significantly and effectively improve the clinical scenario of such complex malignancies.

## Conclusion

Our trial will provide insight into the efficacy and safety of VT-ART through a matched pair analysis, by an observational, multicentric study (with prospective and retrospective data collection) *via* subgroup stratification into dynamic cohorts of two groups of patients with or without VT-ART in a multicentric consortium.

## Ethics statement

This study was reviewed and approved by the Ethics Commission of Fondazione Policlinico Gemelli IRCCS (Rome, Italy). Written informed consent will be obtained from all participants for their participation in this study and every participant center must submit our protocol to their respective ethics commission before enrolling patients.

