	5. LVEF >20%
	6. ICD implant
	7. Signed informed consent
	8. Life expectation >1 year in absence of VT
Exclusion criteria	9. ICD interrogation demonstrating polymorphic VT
	10. Patients with INTERMACS class >4
	11. Patients with LVADs
	12. Patients with ongoing neoplastic disease
	13. Previous thoracic RT with cardiac involvement
	14. Active myocardial ischemia
	15. Cardiac revascularization <120 days

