## Outcome measures

The primary outcome is investigating the difference in overall cardiovascular survival among the group undergoing VT-ART and the one not exposed to the innovative procedure.

The primary efficacy endpoint is a statistically significant difference in overall cardiovascular survival between the group undergoing VT-ART and the one not exposed to the innovative procedure; this will be defined in months and calculated from the time of the last procedure (represented by the last RFA for the control group and VT-ART for the innovative one, respectively).

The secondary outcome is evaluating the difference in ventricular event-free (referred to VT/VF, appropriate shock or ATP as recorded by the ICD) survival after the last procedure between the two groups (i.e., the single or last RFA in the control group and VT-ART in the innovative group). The respective endpoint is a statistically significant difference in ventricular event-free survival (in months) after the last procedure between the two groups.

An additional secondary aim is to evaluate the reduction in the number of VT episodes compared to the pre-treatment period between the two dynamic cohorts that will be investigated.

Ventricular tachycardia recurrence will be defined as evidence of monomorphic VT at ICD interrogation (either self-limiting or terminated by appropriate shock therapy or ATP). The number of VT episodes, defined as VT burden, in the 3 months before and after the procedure will then be compared.

The respective secondary endpoint will be evaluated facing 3 months before the last procedure (i.e., either RFA or VT-ART) and 3 months after.

We did set a blanking period after VT-ART before evaluate the effect on VT burden; in a recent study by Kautzner et al., the authors supported the pre-clinical theorem of myocardial apoptosis (up to 3 months post-stereotactic ablation) followed by a creation of fibrotic lesion (6–9 months post-stereotactic ablation) in the irradiated region (5). Consequently, we propose a 3-month-blanking period after the procedure.

Since a blanking period of 3 months after the procedure will be applied, the secondary endpoint will evaluate the number of VT episodes interval accounted for the last 3 months before the procedure and of the 3–6 months after it.

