#### Sample size

The calculation of the sample size considered followed assumptions:

-A total of 95% confidence level;-The drop-out rate of 10%;-Expected difference between the two treatments for 3-month and 6-month VT burden in terms of overall response rates: 20% higher in arm including VT-ART compared to the control group;-Power of 80%.

To improve clinically adequate balancing, we will enroll two matching paired patients in the group not undergoing VT-ART for each patient who undergoes VT-ART in a 2:1 ratio, favoring a larger proportion of patients not undergoing the innovative procedure (i.e., VT-ART).

Under these hypotheses, to detect a 20% improvement in the VT burden control rate in the VT-ART group vs. the control group, we calculated the sample size (in a 2:1 ratio) upon enrolling 149 patients: 100 in the non-exposed control group and 49 in the VT-ART group. Progressively, on a multicentric basis supervised by the promoting center in the VT-ART consortium, for each VT-ART patient enrollment, a matched pair patient profile according to the predefined features will be shared with the consortium to enroll two similar patients who have not undergone VT-ART. For enrollment into the control group, recruitment of clinical cases from retrospective case series within the multicentric consortium will also be allowed, with the only condition to be not earlier than 5 years from the enrollment of the matched pair patient in the VT-ART group (to avoid the possible influence of a too early approach for standard procedures).

All statistical analyses will be performed using SPSS^®^ version 25.0 software (©Copyright IBM Corporation 1994, 2017).

Due to the potential difficulty of enrolling the patients through the complete match of all matching factors, a protocol rule will be applied through patient’s collection.

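### Signed consent is required of every participant, with no exception for retrospective patients, so if it is signed at enrolment the survival endpoint is inflated in whichever arm is more retrospective

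*Protocol article*

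**What the plan says.** Consent appears in three places of the protocol article, without exception by arm, by mode of data collection or by vital status:

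- Populations, Table 1, lists "7. Signed informed consent" among the inclusion criteria.
- Registration: "Eligible participants who provide consent and meet the inclusion criteria are anonymously registered in the CRF".
- Ethics statement: "Written informed consent will be obtained from all participants for their participation in this study".

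Retrospective patients are admitted in both arms. For controls, Sample size says "recruitment of clinical cases from retrospective case series within the multicentric consortium will also be allowed". The same section then limits how old such a case may be: "with the only condition to be not earlier than 5 years from the enrollment of the matched pair patient in the VT-ART group". Protocol overview also allows VT-ART procedures given before the trial's formal start, provided the required data exist, and gives no look-back limit. It allows prospective as well as retrospective RFA controls.

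Outcome measures defines the endpoint: "The primary efficacy endpoint is a statistically significant difference in overall cardiovascular survival". It is measured in months, with this starting point: "calculated from the time of the last procedure (represented by the last RFA for the control group and VT-ART for the innovative one, respectively". Follow-up runs for 36 months. The article mentions neither delayed entry nor left truncation.

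**The concern.** A retrospective patient's survival clock starts at a procedure that may lie years before the study finds that patient. If the patient must then sign, everyone who died in between is shut out by an eligibility rule. Those who remain bring with them an interval, from procedure to signature, in which they could not have died and still been enrolled, and the plan counts that interval as time at risk. Matching on baseline factors cannot repair this, because selection is on the outcome itself.

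The primary comparison is at stake. The abstract describes the control group as a retrospective selection, and Protocol overview speaks of comparing VT-ART with retrospective series, so the filter probably falls harder on controls. That would make standard care look better than it is and could hide a benefit of VT-ART or make it appear harmful. The same rule covers retrospective VT-ART patients, however, so the net effect depends on the mix in each arm.

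**Working it through.** The plan states no survival figure to reproduce. Its 149 patients rest on a VT-burden response rate and are not affected by this point.

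**Inputs from the protocol.** Look-back of 5 years for controls (Sample size); time zero at the procedure (Outcome measures); 36-month horizon (Follow-up); consent required of all (Table 1, Registration, Ethics statement).

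**Assumptions, not in the document.** Annual mortality a of 5, 10, 15 or 20%, with constant hazard λ = −ln(1−a). Lag from procedure to consent uniform on 0 to L years, with L = 1, 3 or 5. Consent is signed at study enrolment, at the end of the lag.

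**Step 1: survival in a fully retrospective arm.**

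- Share alive at consent: A = (1 − e^(−λL))/(λL)
- True 36-month survival: S = e^(−3λ)
- Naive survival among signers: S/A for L ≤ 3. For L = 5 it is [0.6·e^(−3λ) + (e^(−3λ) − e^(−5λ))/(5λ)]/A.

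At a = 15% and L = 5: λ = 0.1625, e^(−3λ) = 0.6141, e^(−5λ) = 0.4437. A = 0.5563/0.8126 = 0.6846, so 31.5% have died before they could sign. Naive survival = (0.3685 + 0.2097)/0.6846 = 84.5%, against a true 61.4%, an inflation of 23 points.

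| Annual mortality | True 36-month survival | Naive, lag ≤ 1 y | Naive, lag ≤ 3 y | Naive, lag ≤ 5 y | Dead before consent, lag ≤ 5 y |
|---|---|---|---|---|---|
| 5% | 85.7% | 88.0% | 92.5% | 95.3% | 12% |
| 10% | 72.9% | 76.8% | 85.0% | 90.1% | 22% |
| 15% | 61.4% | 66.5% | 77.6% | 84.5% | 32% |
| 20% | 51.2% | 57.1% | 70.2% | 78.4% | 40% |

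Inflation is therefore about 2–6, 7–19 and 10–27 points for the three lag limits.

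**Step 2: the comparison between arms.** Take a = 15%, L = 5 and a true hazard ratio of 1, with follow-up cut at 36 months from the procedure.

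- Retrospective, per enrolled patient: deaths = [(1 − e^(−3λ))/λ − 3e^(−3λ)]/(5A) = (2.3743 − 1.8424)/(5 × 0.6846) = 0.155. Years truly at risk after consent = 0.155/λ = 0.96. Immortal years = {[1 − e^(−3λ)(1 + 3λ)]/(5λ²) + 3(e^(−3λ) − e^(−5λ))/(5λ)}/A = (0.655 + 0.629)/0.6846 = 1.88. Years counted = 2.83.
- Prospective, per enrolled patient: deaths = 0.386; years = 0.386/λ = 2.37.

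With a share s of an arm's enrolled patients retrospective, the naive rate is [0.155s + 0.386(1−s)]/[2.83s + 2.37(1−s)]. This gives 0.163 per year at s = 0, 0.132 at 25%, 0.104 at 50% and 0.055 at 100%.

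| Retrospective share, control / VT-ART | Naive rate ratio, VT-ART/control (truth 1) |
|---|---|
| 100% / 0% | 2.96 |
| 100% / 50% | 1.89 |
| 50% / 0% | 1.56 |
| 25% / 0% | 1.23 |
| equal | 1.00 |
| 50% / 100% | 0.53 |

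With all controls retrospective and no VT-ART patients so, the ratio is about 1.2 at lags up to 1 year and 2.0 up to 3 years.

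**Step 3: the remedy.** In a simulation of 2 million patients at 15% and 5 years, counting risk time only from consent gave a control hazard of 0.163 per year, against a true 0.163.

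**The case against.** The article never says when consent is signed. Consent to data use given at the time of the procedure would satisfy the wording and exclude nobody who later died. The look-back sentence in Sample size calls the 5-year limit the only condition on retrospective cases. Follow-up speaks of extracting data retrospectively, and Toxicity evaluation promises to report all-cause mortality. Waivers for deceased patients are often found in the full protocol or in local approvals, and each centre does go to its own committee.

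Of this, the timing point stands: the bias is conditional on signature at enrolment. The rest is possible but not stated. The look-back sentence limits how old a case may be; it does not lift criterion 7. Nor is this a detail merely left out, since the article positively requires consent of everyone. If a waiver exists, the three consent statements are wrong as printed.

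A reader might go further and infer that control survival is certainly inflated, that the bias always runs against VT-ART, or that the error is of the order of 17–27 points. The document supports none of these. Protocol overview allows prospective controls and retrospective VT-ART patients under the same rule, and no shares are given. The 17–27 points need every control to be retrospective, lags spread over the full 5 years, and an assumed annual mortality of 10–20%.

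**Conclusion.** The point holds in conditional form. As written, the consent rule and the admission of retrospective patients conflict. If signature is taken at enrolment, retrospective patients who died earlier are excluded, and their survivors' immortal time enters the primary endpoint.

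For a fully retrospective arm the inflation of 36-month survival ranges from about 2 to 27 points across the assumptions tried, and is smaller in a mixed arm. In the 15%, 5-year case, a true hazard ratio of 1 would appear as a rate ratio anywhere from about 3.0 to about 0.5 for the mixes shown. The likeliest direction is against VT-ART, because the design describes controls as retrospective, but the document does not fix it. An uncertain direction is no reassurance: the primary result would partly reflect the recruitment mix. All sizes rest on assumed mortality, constant hazard and uniform lags.

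**What to change.** 1. Reconcile Table 1 criterion 7, Registration and the Ethics statement with Protocol overview and Sample size. Signature should apply to prospectively enrolled patients and to retrospective patients who are alive and reachable. Seek ethics approval to include deceased or untraceable retrospective patients in both arms.
2. Have each centre list all consecutive eligible retrospective patients, VT-ART and control, regardless of vital status, before matching.
3. Where a committee refuses, analyse the affected patients with delayed entry, at risk only from the consent date.
4. Report the retrospective share and the procedure-to-consent lag by arm.
5. In Follow-up, state that restricting the final analysis to patients with data at the scheduled time points does not remove from the survival analysis those who died before those time points. Otherwise a second survivor filter remains after consent is mended.

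The cost is an ethics amendment and some analysis wording. Delayed entry also loses person-time: in the 15%, 5-year case only 0.96 of 2.83 counted years per retrospective patient remain within 36 months, about a third. Inclusion regardless of vital status is therefore the better route.
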